## Abstract

**Background:**

Use of acupuncture has widely increased in patients with chronic low back pain. However, the evidence supporting its efficacy remains unclear. In this article, we report the design and the protocol of a multi-center randomized sham-controlled trial to treat chronic low back pain. Our goal is to verify the effect of acupuncture on chronic low back pain.

**Methods/Design:**

This study is a multi-center randomized sham-controlled trial with 2 parallel arms. Participants included in the study met the following criteria: 1) low back pain lasting for at least the last 3 months, 2) a documented ≥ 5 points on a 10 cm visual analog scale for bothersomeness of low back pain at the time of screening and 3) between 18 and 65 years of age. Participants were blinded to the real and sham acupuncture treatments. The real acupuncture treatment group received real acupuncture 2 times a week, during a total of 12 sessions over 6 weeks. The control group received sham acupuncture during the same period. In order to assess the primary and secondary outcome measures, the participants were asked to fill out a questionnaire at the baseline and 6, 8, 12 and 24 weeks after starting the treatments. The primary outcome was measured using the visual analog scale for bothersomeness of low back pain at 8 weeks after the initiation of treatments.

**Discussion:**

The result of this trial (which will be available in 2010) will demonstrate the efficacy of using acupuncture to treat chronic low back pain.

**Trial registration:**

This study is registered with the U.S. National Institutes of Health Clinical Trials registry: NCT00815529

## Background

Chronic low back pain (LBP) is one of the most important public health problems, as well as one of the main causes of disability among adults of working age [1]. More than 50% of adults are bothered by back pain each year and over 70% of adults have suffered from back pain at some time in their lives [2,3].

Although a wide range of standard treatments are available [4], back pain patients are often dissatisfied with conventional medical care [5]. Acupuncture is one of the frequently used methods in patients with low back pain [6]. Especially in Korea, where acupuncture has a much longer tradition than in other countries, low back pain is the first reason that people consult with the Korean Medicine Doctor (KMD) for acupuncture treatment [7]. A number of randomized controlled trials (RCTs) on acupuncture for LBP have already been published [8,9]. However, conclusions regarding the efficacy and effectiveness of acupuncture for this common problem remains contradictory [8,9]. Most of these equivocal results are due to low methodological quality, small sample size, and other factors such as inherent difficulties in the use of controls [8-10]. Acupuncture is complicated to evaluate because it is difficult to isolate the characteristic or specific effects of the technique from the non-specific ones [11]. Some reviews have noted the poor quality of research in this area and have insisted on scientifically rigorous studies [8-10].

In this paper, we propose a randomized, sham-controlled study of patients with chronic low back pain, with a predetermined sample size and appropriate follow-up, which will enable us to investigate the efficacy of acupuncture on chronic low back pain.

## Methods & Design

### Overview

This study is a multicenter, randomized, non-penetrating sham-controlled study. The trial was conducted in the following three hospitals after obtaining permission from the Institutional Review Boards of three institutions: East-West Neo Medical Center of Kyung Hee University, Oriental Medicine Hospital of Sang Ji University, and Kyung Won Incheon Oriental Medicine Hospital. The patients were blinded to group allocation. The outcome assessment and the statistical analysis were performed by professionals who were blinded to the assignment of patients to either real or sham acupuncture (Figure 1).

**Figure 1 F1:**
[figure not shown]
**Study sequence; Process of recruitment, randomization to treatment, and outcome assessment**.

### Study duration

October 2008-June 2010

### Participants

Patients aged between 18 and 65 years with non-radicular chronic low back pain of mechanical origin were recruited.

#### Inclusion criteria

Inclusion criteria were developed mainly to exclude patients with specific or complicated low back pain.

• Between 18 and 65 years of age

• Low back pain lasting for at least the previous 3 months

• ≥ 5 points on a 10-cm visual analog scale for bothersomeness of low back pain at the time of screening

• Intact on neurological examination (e.g., lumbosacral nerve function, deep tendon reflexes, plantar response, voluntary muscle activation, and sensory function)

• Non-specific, uncomplicated low back pain, i.e., ICD-10 (International Classification of Diseases-10) codes:

M51.3   Other specified intervertebral disc degeneration

M54.5   Low back pain

M54.8   Other dorsalgia

M54.9   Dorsalgia, unspecified

S33.5   Sprain and strain of lumbar spine

S33.6   Sprain and strain of sacroiliac joint

S33.7   Sprain and strain of other and unspecified parts of lumbar spine and pelvis

• Participation agreement and signed informed consent

#### Exclusion criteria

• Radicular pain

• Pain mainly below the knee, as clinical outcome is likely to vary

• Serious spinal disorders, including malignancy, vertebral fracture, spinal infection, inflammatory spondylitis, and cauda equina compression

• Patients who previously had spinal surgery or are scheduled to have one during the study

• Other chronic diseases that could interfere with acupuncture treatment effects, including cardiovascular disease, diabetic neuropathy, fibromyalgia, rheumatoid arthritis, dementia and epilepsy

• Chief musculoskeletal pain other than back pain

• Acupuncture treatment for low back pain during the previous month

• Conditions where acupuncture might not be safe, including clotting disorders, administration of an anticoagulant agent, pregnancy, and seizure disorders

• Severe psychiatric or psychological disorder

• Inability to read and write Korean

• Pending lawsuits/receiving compensation due to low back pain

• Patient taking corticosteroids, narcotics, muscle relaxant or herbal medicine to treat low back pain or any medication considered to be inappropriate by the investigator

• Refusal to participate in the trial or informed consent

### Recruitment

Participants were recruited through advertisements in local newspapers, the hospital monthly magazine, on a website and on bulletin boards. If patients were interested in participating, they were asked to answer questions to determine eligibility. If eligible, they were guided through the informed consent process. After written consent was obtained, a study researcher administered the baseline questionnaire followed by random allocation to either the real or sham acupuncture group. After randomization, the interviewer scheduled the treatment procedure.

### Randomization procedures

The patients were randomized per center in order to give each investigator the same chance to use individual, standard, and sham acupuncture to control the selection bias of the trial. The random code for randomization was generated by the medical statistician and was kept by a clinician who did not contact patients.

Randomization was performed only after a subject was confirmed to be eligible and written informed consent was obtained. Subject details were recorded and a treatment arm and randomization number were allocated to the subject, and both of these were recorded in the subject's hospital file. The randomization form will be completed and returned to the principal investigator.

In order to ensure balance within the two groups, blocked randomization was employed. This was made possible by using computer-generated random numbers from SAS software or other computer software. Different block sizes can be used. For a block of four, the possible assignment orders are AABB, ABAB, ABBA, etc. If there is an important predictor of outcome, stratified block randomization is available. For example, gender may be a strong predictor, and then block randomization within each of the two strata, male and female can be performed. The blinding credibility of the real and sham acupuncture treatments were evaluated at the baseline and at the end of the 6-week treatment.

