### Sample size determination

Generally, a level of significance of α = 0.05 and a power of 1-ß = 0.80 were used. For two arms (control - sham acupuncture, experimental - real acupuncture), we considered the two sample t-test model.

Experimental group: real acupuncture

Control group: sham acupuncture

Primary parameter: VAS for bothersomeness at 2 months after beginning of treatment

Expected mean difference and common standard deviation between two groups: 1.5 on a 0-10 VAS for bothersomeness, SD = 2.73

Drop-out rate: 20%

Sample size determination:(1)

where,

*N *: total sample size

*n*_*t *_: sample size for experimental group

*n*_*c *_: sample size for control group

r: number of experimental group

s: number of control group

λ: ratio of experimental and control sample size (λ = *n*_*t*_/*n*_*c*_)

In the trial, r = 1, s = 1 and λ = 1 were assumed, and then *N *= *n*_*t *_+ *n*_*c *_

To determine optimal sample size, we considered the following hypotheses of interest and formulas of sample size

Under hypotheses *H*_0_: μ_c _= μ_t _*H*_1_: μ_c _≠ μ_t _

sample size:(2)

μ_t _: mean of experimental group

μ_c _: mean of control group

σ^2 ^: common variance between two groups

α: probability of type 1 error (significance level)

ß: probability of type 2 error

Z_α/2_: α/2th quantile of standard normal distribution

Z_ß _: ßth quantile of standard normal distribution(3)

μ_c_-μ_t _= 1.5, σ = 2.73(Reference: Cherkin et al)[25]

Using formulas (1) above:(4)

For the equal allocation for the two groups, total sample size considering drop-out rate of 20% was calculated as 130 subjects.

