#### Description of baseline characteristic and homogeneity test of two groups

For the description of baseline characteristics, both demographical and clinical, for all subjects in the clinical trial, the mean with standard deviation, range with minimum and maximum for quantitative data and frequency with percentage for qualitative data are described.

For the homogeneity test of the baseline characteristics, both demographical and clinical, between the two groups, two-sample t-test for quantitative data and Chi-square test for qualitative data were performed. If there were baseline characteristics showing statistical significance and possibility of covariance, ANCOVA (analysis of covariance) was used for analysis and adjustment of baseline characteristics.

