#### Efficacy

##### • Primary variable

The two-sample T-test was used for VAS for bothersomeness of low back pain at baseline and at 8 weeks for the comparison of the two groups and to determine differences from baseline. ANCOVA and two-sample T-test was used between the differences at baseline VAS and 8 week VAS for each groups. Also, a 95% confidence interval was added for all analyses.

Repeated measure two factor analysis will be used to analyze the difference and mean change among baseline, and 4, 6, 8, 12 and 24-week VAS, difference and mean change between groups, and interaction between groups and observed time. If necessary, a mixed model approach was also used.

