### Data handling

Investigators entered the information required by the protocol into the Case Report Forms (CRFs). Non-obvious errors or omissions were entered into data query forms, which were returned to the investigational site for resolution. The data from all centers were gathered and summarized with respect to demographic baseline characteristics, effectiveness and safety observations.

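### Randomisation is blocked within three centres, but the primary test omits centre; if centres differ in outcome, the test is mildly conservative and some precision is lost

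*Protocol article*

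**What the plan says.** All references are to the protocol article.

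- **Design.** The Overview says "The trial was conducted in the following three hospitals". Randomization procedures says "The patients were randomized per center" and "In order to ensure balance within the two groups, blocked randomization was employed". Block size is left open, and gender is mentioned only as a possible further stratum.
- **Primary analysis.** Under Efficacy, Primary variable: "The two-sample T-test was used for VAS for bothersomeness of low back pain at baseline and at 8 weeks". For the change from baseline it adds "ANCOVA and two-sample T-test was used between the differences at baseline VAS and 8 week VAS for each groups". The covariates of that ANCOVA are not listed there.
- **Covariate rule.** The section on baseline description and homogeneity tests says "If there were baseline characteristics showing statistical significance and possibility of covariance, ANCOVA (analysis of covariance) was used for analysis".
- **Sample size.** The calculation rests on the same unstratified test: "we considered the two sample t-test model".

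Centre is not named as a factor, covariate or stratum in any of the analysis sections or in the sample size section.

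**The concern.** Blocking within each hospital makes the arms nearly equal in size there. Differences in mean outcome between hospitals then cancel out of the treatment contrast. A two-sample t-test does not know this: it leaves the between-hospital differences in its pooled variance and reports a standard error larger than the true one. The confidence interval is then wider than it need be, and the test rejects less often than 5% under the null hypothesis.

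The covariate rule does not repair this. It selects on significant imbalance between arms, and centre is the one factor that the design keeps in balance. Followed as written, the rule would practically never bring centre in, however strongly centre predicts outcome. What is at stake is precision and agreement between design and analysis, not bias.

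**Working it through.** **Inputs from the article (Sample size determination):** difference 1.5, SD 2.73, two-sided α 0.05, power 0.80, 1:1 allocation, 20% drop-out.

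**Inputs assumed:** ρ, the share of total outcome variance due to centre, taken as 0%, 2%, 5% and 10%. The article gives no figure. The SD of 2.73 is taken as the total SD, including centre differences, and the arms are taken as balanced within centre among completers.

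**Step 1: reproduce the planned size.** n per arm = 2(1.96 + 0.84)² × 2.73² / 1.5² = 52. With drop-out, 52/0.8 = 65 per arm, or 130 in total. This matches the article.

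**Step 2: standard error.** The t-test reports about 2.73 × √(2/52) = 0.535. With balance within centre, the true standard error is 0.535 × √(1 − ρ). The reported value is therefore too large by the factor k = 1/√(1 − ρ).

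**Step 3: type I error of the t-test.** Approximately 2 × [1 − Φ(1.96k)].

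**Step 4: power at 52 per arm.** Without centre, the true standard error governs the spread of the estimate, but the critical value is scaled by the overstated one. With centre, the residual SD is 2.73 × √(1 − ρ) and the t-test has 104 − 4 = 100 degrees of freedom. For ρ = 5%, the true standard error is 0.522 and the non-centrality is 1.5/0.522 = 2.87.

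| ρ (assumed) | True SE | SE too large by | Type I error, no centre | Power, no centre | Power, with centre | Gain (points) |
|---|---|---|---|---|---|---|
| 0% | 0.535 | 0% | 5.0% | 79.3% | 79.2% | −0.1 |
| 2% | 0.530 | 1.0% | 4.8% | 79.5% | 80.0% | 0.5 |
| 5% | 0.522 | 2.6% | 4.4% | 79.8% | 81.2% | 1.4 |
| 10% | 0.508 | 5.4% | 3.9% | 80.5% | 83.3% | 2.8 |

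Power at ρ = 0 is slightly below 80% because the t distribution is used here, whereas Step 1 uses the normal approximation.

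**Check by simulation** (three centres, 52 per arm, 20,000 runs). At ρ = 5%, type I error was 4.5% without centre and 5.0% with it; power was 80.0% and 81.3%. At ρ = 10%, type I error was 3.8% and 4.9%; power was 80.3% and 83.2%. These agree with the table within simulation error.

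**The case against.** **The loss is conditional and may be nil.** It arises only if centres differ in outcome. The article gives reasons to expect limited differences: all acupuncturists had common intensive training, the points were predefined by consensus, and every patient received the same exercise manual. Individualised point choice applies only to the real acupuncture arm, so it would mainly make the treatment effect vary by centre, which a centre main effect does not remove. This stands, and it is why the range starts at zero.

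**The covariates may be settled elsewhere.** The ANCOVA under Primary variable lists none, a mixed model is allowed if necessary, and a condensed article may leave the list to an analysis plan that is not shown. This weakens the point without defeating it. The article does not merely stay silent: it names a test that cannot contain centre and a covariate rule that would not select it.

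**Stronger readings that the article does not support:**

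- *The primary test is invalid.* A reader might infer this from a type I error that departs from 5%. The departure is downwards, the estimate is unbiased and the interval over-covers, so no false positive claim follows.
- *The trial is the wrong size.* The 130 was computed for the same unstratified t-test with SD 2.73, so it remains adequate for that test.
- *Centre adjustment lifts power from 79% to 83%.* The 79% applies when centres do not differ. At a 10% share the t-test itself reaches 80.5%, because the true variance is smaller, so the gain is 2.8 points.
- *The Data handling section shows that centres are pooled without adjustment.* It describes gathering and summarising data and says nothing about the analysis model.

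**Conclusion.** The point holds as a mismatch between randomisation and analysis, with a small and conditional cost. For an assumed centre share of 0% to 10%, the standard error is overstated by 0% to 5.4%, type I error lies between 5.0% and 3.9%, and power changes by between −0.1 and 2.8 points when centre is added.

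The omission and the unsuitable covariate rule can be read directly from the article. The size cannot: it rests on the assumed shares, on 2.73 as the total SD and on balance within centre among completers. This is a worthwhile improvement in efficiency and not a threat to the validity of the trial's conclusion.

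**What to change.** Make the primary analysis a single pre-specified ANCOVA of the 8-week bothersomeness VAS on treatment, baseline VAS and centre (fixed effect, three levels). Add any other stratum actually used in randomisation, such as gender, and state which strata were used. These terms should enter whatever the baseline significance tests show. Include centre likewise in the repeated-measures or mixed models for the primary and secondary outcomes.

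Centre costs two degrees of freedom and one sentence of text. If centres do not differ, the loss of power is about 0.1 percentage points. The sample size need not change.

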### Education of acupuncturists

Licensed Korean Medicine Doctors (KMDs) who specialize in Korean Rehabilitation Medicine from the three participating hospitals should take the educational course to strictly adhere to the study protocol and to be familiar with administering study treatments; all participating KMDs underwent intensive and customized training for a full understanding of the "sham acupuncture" procedure, including details such as acupuncture points, depth, and manipulation. They were also trained to administer real acupuncture using a sham needle device.

#### Treatment details

Both real and sham acupuncture groups received a total of 10-12 acupuncture sessions (approximately two times a week, for 6 weeks). In the real acupuncture group, disposable sterile needles (40 mm × 0.25 mm) were used (Dong-bang Acupuncture Inc., Seoul, Korea), while non-penetrating sham needles with identical gauge were used in the sham control group (Acuprime Co., Ltd, UK). At the time of the first acupuncture session, all participants received an "exercise manual for low back pain patients" from the spine center of East-West Neo Medical Center of Kyung Hee University and were encouraged to do exercises according to the manual during the whole treatment period. This manual includes information on physical activity, exercise and appropriate life-style modification.

##### • Real acupuncture

A pre-defined, individualized acupuncture prescription in accordance with the characteristics of pain was employed. For this study, we developed a flexible treatment protocol by selecting a group of points that were predefined in every case, allowing the participating KMD some flexibility in the choice according to the diagnosis. The predefined points were carefully selected by a process of consensus with participating KMDs who were all experienced in low back pain. When we treated the patients in this research, we chose acupuncture points after the process of the meridian pattern identification. To treat low back pain, we assumed 3 types of meridian pattern identification according to the pain location (A: Gallbladder meridian pattern, B: Bladder meridian pattern, C: Mixed pattern).

The acupuncture points included: Shenshu (BL23), Qihaishu (BL24), Dachangshu (BL25), Yimmen (BL37), Weizhong (BL40), Wangu (GB12), Daimai (GB26), Huantiao (GB30), Yanglingquan (GB34), Zulinqi (GB41), Dicang (ST4), Zusanli (ST36), Fushe (SP13), Fujie (SP14), Yaoyangguan (GV3), Mingmen (GV4), Xuanshu (GV5), Shenting (GV24) and Shuigou (GV26).

Acupuncture treatment was given using a sterile, disposable stainless steel needle (40 mm × 0.25 mm) with the aid of the tube of a sham acupuncture needle device. After the skin sterilization, the needles were inserted perpendicular to a depth of 5-20 mm with the patient lying down and blindfolded, followed by bidirectional rotation to induce *Deqi *sensation. The needles were left in place for 15-20 minutes.

As the real acupuncture group received treatment that reflects everyday practice, the acupuncture points were varied from visit to visit when the symptoms or pain changed.

##### • Sham acupuncture

Non-penetrating sham needles by Park et al. (Acuprime Co., Ltd, UK)[12] were used. Eight pre-defined points in the lower back, which are non-traditional acupuncture points, were used after skin sterilization, with patients lying down; 1 cm below from Weiyang (BL39), 1 cm lateral to Ganshu (BL18), 1 cm lateral to Pishu (BL20), and 2 cm above from Huantiao (GB30), all bilaterally. The technique did not vary in any way from that performed in the real acupuncture group, except for the usage of a semi-blunted needle. The sham needles were left in for 15-20 minutes of the session, as was done in the real acupuncture group.

### Outcome measurements

Patient completed a series of measurements to assess back pain-related dysfunction, pain, quality of life, and back pain-related costs.

At the screening visit, patients were asked to fill out a questionnaire regarding age, gender, marital status, residence, occupation, and education. Medical history was also taken before physical check-ups and it was determined whether the patient would be included or not. The baseline (T0), 4 (T1), 6 (T2), 8 (T3), 12 (T4), and 24 (T5) week follow-up measurements are summarized in Table 1.

**Table 1 T1:** Schedule for data collection; outcome measures per visits

Measures	Baseline (0-week)	4-week	End of treatment (6-week)	8-week	12-week	24-week
Sociodemographic characteristics	X					
Back pain history	X					
X-ray	X			X		
VAS for bothersomeness of low back pain	X	X	X	X	X	X
VAS for pain intensity	X	X	X	X	X	X
Oswestry disability Index (ODI)	X		X	X	X	X
General health status (SF-36)	X		X	X	X	X
EuroQol-5D (EQ-5D)	X		X	X	X	X
Beck Depression Inventory (BDI)	X		X	X	X	X
Medication use	X		X	X		
Costs of back care	X		X	X		X
Adverse experiences*	X	X	X			
Credibility test†	X		X			
Acupuncture experience (In-depth interview)§				X		

*, At every single visit; †, After 1st treatment and at the end of treatment (6-week); §, 10 randomly chosen participants (5 from acupuncture group and 5 from sham group) for each hospital, thus 30 in total.

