### Protection of subjects and assessment of safety

Any adverse experiences at any clinic visit during the 12 sessions were monitored. The research team monitored serious adverse experiences, which were defined as treatment-related experiences.

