#### Safety

All adverse effects were recorded and described as frequency and percentage. For the comparison of adverse effects between groups, the Chi-square test or Fisher's exact test were performed.

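### Adverse experiences are scheduled only for the 6-week treatment period, although assessments run to week 24 and the between-arm safety comparison names no time window

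*Protocol article*

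**What the plan says.** Four places in the protocol article bear on this.

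- **Outcome measurements, schedule.** The text reads "The baseline (T0), 4 (T1), 6 (T2), 8 (T3), 12 (T4), and 24 (T5) week follow-up measurements are summarized in Table 1". The table is titled "Schedule for data collection; outcome measures per visits", so weeks 8, 12 and 24 stand as visits in the schedule.
- **Table 1, adverse-event row.** The row "Adverse experiences" is marked at baseline, week 4 and week 6. The last three columns are blank. Its footnote reads "At every single visit".
- **Protection of subjects and assessment of safety.** "Any adverse experiences at any clinic visit during the 12 sessions were monitored". The treatment details place those sessions in the first six weeks: both groups "received a total of 10-12 acupuncture sessions (approximately two times a week, for 6 weeks".
- **Safety, under the statistical methods.** "All adverse effects were recorded and described as frequency and percentage". The next sentence adds the test: "For the comparison of adverse effects between groups, the Chi-square test or Fisher's exact test were performed". Neither sentence gives a period.

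**The concern.** Two of these places set a collection window that closes with treatment. The other two set none. A reader of the Safety section cannot tell whether the frequencies and the test refer to six weeks or to 24.

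At stake is the content of the safety comparison. The trial compares penetrating needling with a non-penetrating sham. Events that begin after the last session, or that have not resolved by then, are part of the harm profile of the real arm, and a fair comparison asks about them in the same way in both arms. If nobody asks after week 6, such events enter the data only by chance. An analysis plan cannot repair this later, because it cannot recover information that was never collected.

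The point concerns safety reporting only. The primary efficacy analysis and the sample size do not depend on it.

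**Working it through.** The plan states no figure for this point that could be reproduced, so the check is a comparison of the schedule entries, with simple counts.

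**Step 1: the places side by side**

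| Place | Window it gives |
|---|---|
| Table 1, marks in the row | Weeks 0, 4 and 6 |
| Table 1, footnote | Every visit, no limit stated |
| Protection of subjects | Clinic visits during the sessions, so to week 6 |
| Safety (statistics) | All adverse effects, no period stated |

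The marks and the subject-protection section agree on a treatment-period window. The footnote can be read either way. The Safety section is silent.

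**Step 2: calendar time without scheduled collection**

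Inputs: end of treatment at week 6, last assessment at week 24 (Table 1).

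(24 − 6) / 24 = 18 / 24 = 75% of follow-up.

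**Step 3: scheduled contacts**

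- Table 1 columns with a mark: 3 of 6.
- Post-baseline columns without a mark: 3 of 5 (weeks 8, 12 and 24). Week 8 is the primary endpoint.
- These column counts leave out the 10-12 treatment sessions at which adverse experiences were monitored. Assume that the week 4 and week 6 assessments coincide with sessions. The post-baseline contacts are then the sessions plus three later assessments:
  - 10 sessions: 10 / (10 + 3) = 10/13 = 77% of contacts have collection.
  - 12 sessions: 12 / (12 + 3) = 12/15 = 80% of contacts have collection.

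Most contacts are therefore covered, but most of the calendar time is not.

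**Step 4: what else is measured after week 6 (Table 1)**

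| Measure | Week 8 | Week 12 | Week 24 |
|---|---|---|---|
| VAS bothersomeness, VAS pain intensity | yes | yes | yes |
| ODI, SF-36, EQ-5D, BDI | yes | yes | yes |
| Medication use | yes | no | no |
| Costs of back care | yes | no | yes |
| Adverse experiences | no | no | no |

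Back pain, function, quality of life and depressive symptoms are followed to week 24 in both arms. What is left uncovered is any late or persisting event that these scales do not register. The documents give no rate for such events, so their number cannot be estimated.

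**The case against.** The strongest reply is that the article describes one consistent window. The table has columns only for selected weeks, while treatment was given about twice weekly. The footnote then explains that the marks stand for every treatment visit and not just the column weeks. The neighbouring footnote on the credibility test works in the same way: it moves a mark in the baseline column to the time after the first treatment. On this reading the table, its footnote and the subject-protection section all agree. A treatment-period window for a six-week intervention is an open choice, and a condensed article may leave the handling of unresolved events to the full protocol.

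Much of this stands. It rules out four stronger readings that a reader might infer:

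- **That the plan flatly contradicts itself.** The footnote has a natural reading that fits the marks. It is ambiguous, not provably in conflict.
- **That worsening back pain after treatment goes unrecorded.** Both VAS scales, the ODI and the SF-36 are taken at weeks 8, 12 and 24. Only its recording as an adverse event would be lost.
- **That three of five post-baseline assessments without collection means that most contacts are uncovered.** The count ignores the 10-12 sessions.
- **That the Safety section promises 24-week coverage.** Its wording is general and is compatible with all effects found under the stated monitoring.

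The reply does not supply the missing window in the Safety section. If its reading is right, it also confirms that no adverse-experience question is scheduled after week 6, although participants are assessed three more times.

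**Conclusion.** The point holds in a limited form. As marked in Table 1 and described in the subject-protection section, adverse-experience collection ends with treatment at week 6. The between-arm comparison then covers the treatment period only, and the Safety section does not say so. The uncovered span is 18 of 24 weeks. What may be lost in it is the set of late or persisting events that the VAS, ODI, SF-36, EQ-5D and BDI do not capture. How many there would be is unknown from the documents, and the 75% is a share of time, not of expected events, since no study needling takes place after week 6.

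This rests on two assumptions: that the table marks reflect what was done, and that the full protocol does not extend collection. If the footnote was meant literally and data were taken at all visits to week 24, there is no gap in collection, and the remaining task is to correct the marks and the subject-protection text. Under either reading some wording has to change. It is worth doing as a cheap improvement to safety reporting; it does not threaten the trial's main conclusion.

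**What to change.** - Add the same open adverse-experience question in both arms at the existing week 8, 12 and 24 assessments.
- Mark those columns in Table 1, reword the footnote so that it says which visits it means, and extend the subject-protection section to the same window.
- In the Safety section, name the period and report 0-6 weeks and 0-24 weeks separately by arm.
- If collection did end at week 6 and cannot be extended, state in the Safety section and in the results that the comparison covers the treatment period only.

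The cost is one short item at three assessments that already take place. Week 8 includes an X-ray, so attendance is expected there. Weeks 12 and 24 list mainly self-report measures, and in-person contact is not spelled out, so the item may have to be self-reported at those times. The 0-24 week table will also pick up some background events unrelated to treatment, which is why the two periods should be shown separately. If only the wording is changed, there is no data-collection cost.
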